### Randomization, Allocation, and Masking

After confirming eligibility and informed consent, participants are randomly stratified by HI severity and the field site to ensure a balanced distribution of participants. Randomization is performed by an independent statistician who is not involved in data collection, management, or analysis using a computer-generated random number sequence to assign participants to either the treatment or control group [35]. Allocated interventions will not be modified unless participants voluntarily withdraw for personal reasons. Due to the nature of the interventions, complete blinding of participants and facilitators is not feasible. However, we minimize the potential biases by blinding participants to the study hypothesis, using standardized protocols for training and tools for measurement, and masking field staff to allocation details.

### Study Interventions

The community-delivered interventions are developed based on the conceptual framework of ICF and the stress-buffering model. The HAU group mainly targets addressing HI as a stressor or physical impairment and improving personal resources for managing HI. The HHE group aims to eliminate or minimize the social effects of HI by enhancing awareness, acceptance, adaptation, and support for HI through personal and social resources among adults with HI.

#### Hearing Rehabilitation Intervention: Hearing Aid Use Group

Participants in the hearing rehabilitation intervention treatment group are fitted with bilateral or unilateral hearing aids. The hearing aids are fitted to participants in accordance with the protocol established by the hearing aid manufacturer and the guidelines launched by CDPF with professional audiologists. Instructions on the usage of hearing aids, the proper insertion of the aids and batteries, and a comprehensive, step-by-step guide on their usage and maintenance, are also provided. Materials for self-management and adaptation strategies are also explained and provided after the fitting services. To improve hearing aid compliance, support is offered after fitting (1 month later) to ensure that each participant is progressing with their hearing aids. In addition, a WeChat (Tencent) group has been established for HAU participants and audiologists to address sporadic needs from hearing aid users, such as battery replacements, cleaning, or proper storage of hearing aids. Unscheduled interim visits are necessary for troubleshooting or repairing malfunctioning hearing aids or addressing other related issues if the problem cannot be resolved through online or telephone communication. Postintervention reinstruction on the use of hearing aids is conducted 12 months after the fitting through telephone communication and the dissemination of digital materials via the WeChat group.

#### The HHE Intervention

The HHE intervention group is developed based on the Health Education Services Standard of the National Basic Public Health Service Standard (third edition), a national guideline issued by the National Health Commission of the People’s Republic of China for guiding health education for community-dwelling residents [36]. It targets participants with HI, their CPs or family members, community residents, and hearing health–related community workers (ie, social workers, local staff of CDPF, and civil affairs). The objectives of HHE include improving awareness, knowledge, and literacy of hearing health among individuals, families, and communities, developing communication strategies and skills for adults with HI and their CPs or family members, as well as creating a supportive family and community environment that promotes social inclusion and accessibility to hearing health care services.

The HHE intervention consists of three parts. Part A is an interactive, face-to-face session consisting of a hearing health lesson and counseling for participants with HHE and community workers. Brochures for participants and their CPs or family members, and posters for community health education boards are provided. The hearing health lesson is taught by the program coordinators with a written lesson plan and prepared with easily accessible teaching materials, such as paper-based visual aids or slides. Part B is an internet-based educational section that aims to reinforce the content covered in Part A through the use of the WeChat public account. It was conducted 6 months after the baseline survey targeted adults with HI and their CPs. Part B consists of a 2-week online information support program delivering knowledge on hearing health and its consequences, positive skills and strategies for interacting with adults with HI, hearing prevention and rehabilitation guidance, and social support for adults with HI through textual, image, and video formats. All interventional-related information is disseminated through the WeChat public account registered by the research team. To ensure the accessibility and reach of online information support, the research team set up a check-in task and regularly reminded the procedure. Part C is an offline information provision that was conducted 12 months after the baseline survey with the purpose of reinforcing content in Part A and Part B. Hearing health educational pamphlets are designed for all the intervention objectives and are delivered to them accordingly. The content presented in the lessons, brochures, posters, a WeChat public account, and pamphlets is based on and adapted from the WHO Hearing Report (2021) and other relevant publications [37,38]. During the design phase of the intervention, the HHE intervention settings were discussed and deliberated with experienced audiologists, community workers, and community-dwelling adults with HI who would not participate in the study. It is deemed acceptable for adults with HHE and their CPs in the community.

### Control Group

No interventions are provided for the control group considering the current situation of the HI rehabilitation:

Firstly, the prevalence of hearing aid usage in China is notably low, and there is a lack of health care awareness among rural older adults experiencing HI. A population-based survey carried out between 2014 and 2015 across 4 provinces in China, including Guangdong, revealed that the estimated prevalence of hearing aid acquisition among rural older adults with hearing loss is 4.2%. The reasons for not having a hearing aid within this group included “not understanding its function,” “not being able to afford it,” and “not needing it” [39]. According to the China Health and Retirement Longitudinal Study 2018 data, only 3% of older adults in rural areas with subjective hearing loss self-reported experience of using hearing aids [40]. Both sets of data indicate that they resonate with the natural setting for the control group.

Secondly, the policy context in Guangdong Province requires the attainment of a disability status qualification before the application for government-subsidized hearing aids, potentially discouraging older adults with HI from initiating the application process. The government offers subsidized hearing aids at institutions specifically established to provide services related to assistive devices for individuals with hearing disabilities. However, it is essential for these individuals to actively secure an official assessment to obtain a disability certificate, which is a prerequisite for applying for subsidized hearing aids. The process of obtaining disability status may be associated with social stigma, which could inhibit individuals from applying despite the availability of government subsidies. Therefore, the number of disabled individuals seeking these hearing aids remains relatively low.

Considering these 2 points, we have opted not to intervene with the older adults in the control group. Participants who are eligible for the control group are required to engage in both the baseline and follow-up surveys.

### Outcome Measures

This study investigates the 24-month impact of HAU and HHE interventions on social isolation, functioning, and engagement among adults with HI and further explores the buffering role of psychosocial factors in these outcomes. The detailed outcomes are listed in Textbox 2.

Outcome measures.
**Primary outcome measures**
Social isolation, assessed by the abbreviated 6-item Chinese version of the Lubben Social Network Scale (LSNS-6), which has been recognized as a good tool to screen for social isolation among community-dwelling adults by several cross-national and cross-cultural validation studies [41,42]. The LSNS-6 evaluates one’s perceived social network or support received from family and friends.Functioning, measured by World Health Organization Disability Assessment Schedule 2.0 (WHODAS 2.0), evaluates an individual’s health-related functioning and disability across 6 life domains within the International Classification of Functioning, Disability and Health (ICF) framework [34]. WHODAS 2.0 is a cross-culturally valid tool that reflects a person’s ability to participate in daily life activities (personal perspective: cognition, mobility, and self-care) and to engage with their environment (social perspective: getting along, life activities, and participation).Social engagement, determined through a subjective assessment using the 6-item Index of Social Engagement (ISE), which describes an individual’s self-evaluation of both social involvement and autonomy, is used to capture subjective social engagement [43], and objective evaluations via the 10-item Social Engagement and Activities Questionnaire (SEAQ).

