**Methods:**

This study is a 3-arm, single-blinded, randomized controlled trial (RCT) with a follow-up at 24 months after the baseline study. A total of 435 participants aged 18 years and older with some degree of HI will be recruited and randomly assigned to 2 intervention groups and 1 control group. Free hearing-aid provision, as well as a hearing health education program that is combined with online and offline lessons, will be implemented in 2 intervention groups, respectively. The control group will not receive any intervention. The primary outcomes include social isolation and functioning in society. The secondary outcomes include social engagement, a sense of mastery, self-efficacy, psychological resilience, chronic diseases, life satisfaction, hearing health literacy, and hearing care usage.

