### Study Aims and Hypotheses

This full-scale randomized controlled trial (RCT) aims to evaluate the feasibility and efficacy of a community-delivered hearing aid provision and HHE program in improving social health among hearing-impaired adults in China. The key outcomes are social isolation and societal functioning. In addition, it seeks to determine if psychosocial factors and social support buffer the HI-SWB linkage as well as the effects of hearing interventions on social health.

We hypothesize there will be positive effects after the long-term interventions of HAU and HHE on hearing-impaired older adults’ social health, and strengthened psychological well-being could be potential pathways.

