### Study Design and Setting

A three-arm, single-blinded RCT with a 24-month follow-up period will be conducted. A total of 435 eligible participants were randomly assigned in a 1:1:1 ratio to a control group, a hearing aid use (HAU) group, or an HHE group. The HAU group will receive hearing aids and follow-up instructions. Due to budget constraints, the audiological rehabilitation intervention predominantly used hearing aids provided by the Audiology Department of the Guangdong Provincial Cultural Sports and Rehabilitation Assistive Devices Center for People with Disabilities (GPSRC), which is affiliated with the China Disabled Persons’ Federation (CDPF). Individuals diagnosed with disabling HI and classified as persons with hearing disability are eligible to apply for complimentary hearing aids and fitting services from the local CDPF departments. Since the number of adults with HI who were eligible for hearing-aid fitting was limited to one site at the time of the baseline survey and intervention, a total of 139 persons with disabled HI were randomly selected from 4 sites with similar socioeconomic and cultural conditions. The selection was based on the list provided by GPSRC, which maintains records of hearing-disabled persons in Guangdong Province. The HHE group will undergo both offline and online educational interventions, while no interventions are planned for the control group that is similar to a natural setting. A sample of 278 adults diagnosed with some degree of HI was randomly selected and assigned to the HHE group and control group from Hualong County in Guangzhou, Guangdong, based on its roster. For the HAU group, participants were prescribed hearing aids at baseline (T0) and received reinstruction on the use of hearing aids 12 months after T0. For the HHE group, participants were required to participate in an offline hearing education at T0, followed by an online educational intervention at 6 months after T0, and an offline information intervention at 12 months after T0. The primary outcomes are social isolation and functioning, assessed at baseline and 24 months.

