### Sample Size Calculation and Recruitment

Sample size calculations are based on the expected effects of the hearing aid intervention on the primary outcome: an individual’s functioning in society measured by the World Health Organization Disability Assessment Schedule 2.0 (WHODAS 2.0), which was developed within the ICF conceptual framework [34]. We estimate that a sample size of 222 (111 participants in each group) provides 85% statistical power with a 5% significance level to detect a standardized effect size of 0.404 for the difference between the HAU group and the control group in the mean change from baseline in the functioning score at the 24-month follow-up [23]. Since there is little evidence evaluating the effects of HAU on social isolation using the Lubben Social Network Scale (LSNS), or the effectiveness of HHE on functioning and social isolation, we will assign the HHE group the same sample size as the HAU group and the control group. To account for a 20% drop-in (uptake of hearing aids in the control group) and dropout (discontinuation of HAU in the hearing intervention group) rate, a total of 435 individuals are included. This comprises 121 individuals in the HAU group, 158 in the HHE group, and 156 in the control group, respectively. Recruitment activities are conducted in communities and villages (n=8) from Guangzhou, Shanwei, Chaozhou, and other areas in Guangdong Province, China. The recruitment of participants commenced on September 1, 2022, and was completed on September 31, 2022. Oral informed consent is obtained through prescreening, and written informed consent is presented by the investigator to the participant before the hearing screening. Hearing screening and assessment will be undertaken by an audiologist following a standardized procedure (Table 1).

**Table 1 table1:** Schedule of enrollment, interventions, and assessments.

Time point				Study period																												
				Enrollment T_1_						Allocation T_0_					Postallocation T_1_							Postallocation T_2_						Close-out T_4_				
				–30 to –1 Day						Day 0					6 months							12 months						24 months				
				T^a^		T^b^		C^c^		T	T		C		T		T		C		T			T		C	T			T		C
Enrollment																																
Eligibility screen				✓		✓		✓																								
Informed consent				✓		✓		✓																								
Demographics				✓		✓		✓																								
Health history				✓		✓		✓																								
Visual status				✓		✓		✓																								

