Allocation										✓	✓		✓																			
Interventions																																
Hearing aids provision										✓											✓						✓					
Hearing health education											✓						✓							✓						✓		
Assessments																																
Sociodemographics										✓	✓		✓														✓			✓		✓
Hearing outcomes																																
Pure-tone audiometry										✓	✓		✓																			
HHIA^d^ score										✓	✓		✓														✓			✓		✓
Self-reported hearing										✓	✓		✓														✓			✓		✓
IOI-HA^e^ score																											✓					
Hearing-related health literary										✓	✓		✓														✓			✓		✓
Communication ability											✓		✓														✓			✓		✓
SWB^f^ (primary outcome)																																
LSNS-6^g^ score										✓	✓		✓		✓												✓			✓		✓
WHODAS 2.0^h^ score										✓	✓		✓		✓												✓			✓		✓
ISE^i^ score										✓	✓		✓		✓												✓			✓		✓
SEAQ^j^ score										✓	✓		✓		✓												✓			✓		✓
Secondary outcomes																																
GSE^k^ score										✓	✓		✓														✓			✓		✓
PMS^l^ score										✓	✓		✓														✓			✓		✓
CD-RISC^m^ score										✓	✓		✓														✓			✓		✓
EQ-5D-5L score										✓	✓		✓														✓			✓		✓
SWLS^n^ score										✓	✓		✓														✓			✓		✓
Covariates										✓	✓		✓														✓			✓		✓
Lifestyle behaviors										✓	✓		✓														✓			✓		✓
Chronic diseases										✓	✓		✓														✓			✓		✓

^a^T: hearing aid intervention group.

^b^T: hearing health education intervention group.

^c^C: control group.

^d^HHIA: Hearing Handicap Inventory Screening Questionnaire for Adults.

^e^IOI-HA: International Outcome Inventory for Hearing Aids.

^f^SWB: social well-being.

^g^LSNS-6: Lubben Social Network Scale.

^h^WHODAS 2.0: World Health Organization Disability Assessment Schedule 2.0.

^i^ISE: Index of Social Engagement.

^j^SEAQ: Social Engagement and Activities Questionnaire.

^k^GSE: General Self-Efficacy Scale.

^l^PMS: Pearlin Mastery Scale.

^m^CD-RISC: Connor-Davidson Resilience Scale.

^n^SWLS: Satisfaction with Life Scale.

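### The article defines two different primary outcome sets (two measures or four), and its stated 5% level and 85% power cover only one outcome and one contrast

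*Protocol article*

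**What the plan says.** Three places name two primary or key outcomes.

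- Abstract, Methods: "The primary outcomes include social isolation and functioning in society". Its next sentence puts social engagement in the other tier: "The secondary outcomes include social engagement, a sense of mastery, self-efficacy, psychological resilience".
- Study Aims and Hypotheses: "The key outcomes are social isolation and societal functioning".
- Study Design and Setting: "The primary outcomes are social isolation and functioning, assessed at baseline and 24 months".

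Two places name more.

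- Textbox 2, under the primary heading, lists social isolation, functioning and a third entry: "Social engagement, determined through a subjective assessment using the 6-item Index of Social Engagement (ISE". That entry adds an objective scale, SEAQ.
- Table 1 places LSNS-6, WHODAS 2.0, ISE and SEAQ together under "SWB^f^ (primary outcome", with a separate block for secondary outcomes below.

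The opening sentence of Outcome Measures also lists engagement beside isolation and functioning, without assigning a tier.

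Sample Size Calculation and Recruitment rests on the WHODAS 2.0 functioning score for hearing aid use (HAU) against control, and says that 111 per group "provides 85% statistical power with a 5% significance level to detect a standardized effect size of 0.404". It gives the hearing health education (HHE) arm the same size because evidence is scarce for LSNS and for HHE on either outcome. Statistical Analysis names ANOVA and linear mixed-effects models for the differences between control and intervention groups on primary and secondary outcomes.

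**The concern.** One outcome cannot be both primary and secondary. A full protocol or SAP could say which tier is meant, but it could not make both statements in this article true.

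The ambiguity matters because of timing. Trial Status reports that the 24-month survey took place in September 2024 with 397 participants, and the current version is dated January 15, 2025. Both definitions therefore stand in a version written after data collection. If the results favour social engagement, Textbox 2 supports calling it primary. If they do not, the abstract supports calling it secondary.

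The second issue is what the stated error rate and power describe. A reader who sees 5% and 85% beside a list of primary outcomes may take them as properties of the trial's main conclusions. They were calculated for one outcome and one contrast.

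**Working it through.** **Step 1: the plan's own figure.** Inputs from the sample size section: standardized effect 0.404, 5% level (sidedness not stated), 85% power. With a two-sided test,

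n per group = 2 × (1.960 + 1.036)² / 0.404² = 110.02, rounded up to 111.

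The t-based solution is 110.99, also 111, so the total is 222, as stated. A one-sided test would need 89 per group. The figure is therefore a two-sided calculation for one contrast on one outcome.

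**Step 2: possible primary comparisons.** There are two intervention arms and one control, hence two contrasts against control.

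| Reading | Primary measures | Pairwise comparisons |
|---|---|---|
| Abstract, aims, design | LSNS-6, WHODAS 2.0 | 2 × 2 = 4 |
| Textbox 2, Table 1 | plus ISE, SEAQ | 4 × 2 = 8 |

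Step 1 covers one of these 4 or 8. The four exist without any contradiction; only the move from 4 to 8 comes from it.

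**Step 3: conditional illustration of family-wise error.** Assume each pairwise comparison is tested at two-sided 5% and no effect exists. If all tests were independent:

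- 4 tests: 1 − 0.95⁴ = 18.5%
- 8 tests: 1 − 0.95⁸ = 33.7%

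The two contrasts share a control group, so independence cannot hold. With equal arms their correlation is 0.5. With the actual sizes (121 HAU, 158 HHE, 156 control) it is √[(121/277) × (158/314)] = 0.47. A multivariate-normal simulation with 500,000 draws and contrast correlation 0.5 gives:

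| Outcome correlation (assumed) | 4 tests | 8 tests |
|---|---|---|
| 0 | 17.2% | 31.8% |
| 0.3 | 16.9% | 29.9% |
| 0.5 | 16.1% | 26.8% |
| 0.7 | 14.9% | 22.7% |
| 0.9 | 12.6% | 16.5% |

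The documents give no outcome correlation, so these rows show a range and not an estimate. If each outcome were instead tested by one three-group ANOVA, there would be 2 to 4 tests, and 1 − 0.95² = 9.8% to 1 − 0.95⁴ = 18.5% under independence.

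**Step 4: cost of sharing the 5% over four comparisons.** The strictest Holm step is 0.05/4 = 0.0125, two-sided critical value 2.498. With 111 per arm the expected test statistic is 0.404 × √(111/2) = 3.010, so power is Φ(3.010 − 2.498) = 69.6%. The t-based value is 68.8%.

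**The case against.** The strongest reply concerns multiplicity. This is a condensed article, and handling of multiple testing is commonly left to a full protocol or SAP, neither of which is shown. The Statistical Analysis section sets no per-test level, correction, testing order or rule for success, and it does not say that tests will be unadjusted. It does not fix pairwise testing, and an omnibus ANOVA per outcome would halve the count. Whether two distinct interventions need joint adjustment is itself a choice. All of this stands.

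A reader might infer that the trial will run four to eight unadjusted tests, count any one as success, and so carry an error rate of up to 34%. The documents do not support that. The 34% requires independence, which the shared control rules out, and both the lack of adjustment and the success rule would be read from silence.

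A reader might also infer that the primary set is being chosen by result. Trial Status says that the intervention effects were still unknown at this version, and registration is dated before recruitment, although the registered outcomes are not visible here. Selective choice is possible but not shown.

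Finally, only the abstract explicitly calls social engagement secondary; the aims and design sections merely omit it. That is correct, but one explicit contradiction with Textbox 2 and Table 1 is enough. None of these replies removes the conflict.

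**Conclusion.** The primary outcomes are inconsistently defined in the current text: two measures in the abstract, aims and design, four in Textbox 2 and Table 1. This rests on the wording alone and needs no assumption. It is also certain that the stated 5% and 85% describe WHODAS 2.0 for HAU against control, one of 4 or 8 possible primary pairwise comparisons.

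The error rates are illustrative only. They hold if every pairwise comparison is tested at 5%: about 15-17% for 4 tests and 23-32% for 8, at outcome correlations of 0.7 to 0. They would be lower with stronger correlation, or with one omnibus test per outcome at the same correlation. The absence of an adjustment rule from the article is not part of the finding.

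The point should be corrected before analysis, because the choice of set decides which result can carry the trial's main claim.

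**What to change.** Before unmasking:

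1. Keep WHODAS 2.0 and LSNS-6 at 24 months as the primary outcomes, following the abstract, aims and design sections and the sample size basis. Move ISE and SEAQ to secondary in Textbox 2 and Table 1, and align the opening of Outcome Measures.
2. State which outcomes and contrasts carry the 5% level.
3. State that the 85% power applies only to WHODAS 2.0 for HAU against control.
4. If the four primary comparisons are to share 5%, name the procedure. Holm is one suitable option.

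Items 1 to 3 cost only wording, dated before results are seen. Item 4 costs power: about 69% at the strictest Holm step with 111 per arm, which should be reported. No new data are needed.
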